**Methods/design:**

This prospective, cluster-randomised, single-blind, parallel-group, multicentre trial evaluates the morbidity and consequent socio-economic costs of the management of patients experiencing an HAE attack by a dedicated call centre as compared to usual practice. The trial aims to recruit 200 patients. Patients in the intervention arm are provided with an SOS-HAE card with the call centre’s freephone number that they can access in the case of an attack. The centre’s mission is to provide recommended expert advice on early home treatment. The centre can route the call to a local emergency medical service with competency in HAE management or even arrange for the drugs needed for the specific treatment of an HAE attack to be sent to the emergency department of the local hospital. The primary outcome measure is the number of hospital admissions for an HAE attack. Each patient will be followed up every 2 months for 2 years. The study has been approved by the ethics committee (*Comité de Protection des Personnes d’Ile de France 10*; registration number: 2012-A00044-39; date of approval: 19 January 2012).

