### Study population

Eligible patients are adults (≥18 years) with HAE at one of the eight participating reference centres. Inclusion criteria are a documented diagnosis of HAE (type I, II or FXII-HAE) and signed informed consent. Exclusion criteria are pregnancy, recent history (≤1 month) of myocardial infarction or ischemic stroke and allergy to icatibant or plasma-derived C1-INH.

Withdrawal of the study: withdrawal of consent follow-up.

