### Randomisation

The randomised units are the reference centres (clusters) with randomisation stratified according to the number of eligible HAE patients by reference centre. Using permuted blocks of 4, we randomly assigned reference centres (not patients) to the intervention or to usual practice (1:1 ratio).

A modified version of Zelen’s method involving a two-step informed consent process was used for randomisation and inclusion [18]. Eligible patients were first invited to participate in a cohort study but without being informed of the nature of the study arms. Patients who agreed to participate in the study signed the first consent form. This was followed by verification of eligibility (compliance with inclusion/exclusion criteria) and centre randomisation. The patients in each centre were then offered inclusion in the arm assigned to their centre but without being informed of the nature of the other arm. Patients who agreed to be included signed the second consent form. The patient inclusion day is study day zero (D0).

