### Sample size calculation

The aim of this study is to demonstrate a difference in outcome between a methodical management strategy and usual practice. Our primary hypothesis is that an SOS-HAE call centre might benefit patients suffering from an angioedema attack. The sample size calculation is based on the primary outcome, i.e. on the number of admissions for angioedema attacks.

A recent study involving 193 patients with HAE in France reported a rate of approximately 8 attacks/year/patient with approximately 11 % of patients coming to the ED or being admitted to hospital (i.e. an estimated 88 % per year). We hypothesise that implementation of the SOS-HAE call centre management strategy should reduce this rate by 20 %, resulting in a rate of 68 % of ED visits or admissions per year over a 2-year period. If we consider the design effect due to cluster randomisation as relatively low (1.4), the estimated required sample size is 100 patients/arm for 85 % power and a 5 % alpha risk (two-sided comparison).

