#### Analysis of primary outcome

The number of admissions for angioedema attacks will be analysed in the intent-to-treat population.

Because some patients may be blood relatives and because data from within the same family are not independent, the analysis will use generalised mixed models with the family included in the model as a random effect, the strategy as a fixed effect and with a binomial distribution of the variable of interest.

All tests will be two-sided.

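### The 100 patients per arm are used up by 88% v 68% and the design effect of 1.4, so the stated 85% power has no allowance for withdrawal over 2 years, and the scope of 1.4 is not shown

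*Protocol article*

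**What the plan says.** The Sample size calculation section takes a control rate of 88% per year, obtained from about 8 attacks per patient per year and "approximately 11 % of patients coming to the ED or being admitted to hospital (i.e. an estimated 88 % per year"). The call centre "should reduce this rate by 20 %, resulting in a rate of 68 % of ED visits or admissions per year over a 2-year period". A single inflation follows: "If we consider the design effect due to cluster randomisation as relatively low (1.4), the estimated required sample size is 100 patients/arm", with 85% power and a two-sided 5% level. No intra-centre correlation, centre size, variation in centre size or withdrawal rate is given.

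Four other places bear on this figure:

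- Abstract, Methods/design: "The trial aims to recruit 200 patients", each followed for 2 years.
- Study population: withdrawal is foreseen, in the fragment "withdrawal of consent follow-up".
- Randomisation: the eight reference centres are the clusters, with "randomisation stratified according to the number of eligible HAE patients by reference centre".
- Analysis of primary outcome: family is the random effect of the primary model, "Because some patients may be blood relatives and because data from within the same family are not independent".

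**The concern.** A number required for a given power is the number whose outcome is available for analysis. If the recruitment target equals that number, every patient lost takes power below the stated figure. Here the target equals the requirement exactly, follow-up lasts 2 years, and withdrawal is provided for.

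The single factor of 1.4 raises a second question. The plan asserts that relatives' data are correlated, and stratifying by centre size makes sense only if the centres differ in size. Both features can inflate variance, yet the factor is tied only to cluster randomisation and has no derivation.

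At stake is how a null result is read. A non-significant comparison would be taken to come from a trial with 85% power, when that figure assumes complete data on every recruit and rests on a design effect whose content is unknown.

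**Working it through.** **Inputs from the document.** p1 = 0.88, p2 = 0.68, two-sided alpha 0.05, power 0.85, design effect (DE) 1.4, 100 per arm (Sample size calculation); 200 recruited (Abstract); 8 centres (Participating centers). The two rates are taken as proportions, as the plan's figure requires.

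**1. Reproduce the plan's number.** With unpooled variance:

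n = (1.960 + 1.036)² x (0.88 x 0.12 + 0.68 x 0.32) / 0.20²
= 8.978 x 0.3232 / 0.04 = 72.5 per arm.

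Times 1.4 this is 101.6, so 102 per arm. The stated 100 is reproduced to within two patients. The two proportions and the 1.4 account for all of it.

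**2. Power at 100 per arm.** Effective n = 100 / 1.4 = 71.4. The standard error is √(0.3232 / 71.4) = 0.0673, so the standardised difference is 0.20 / 0.0673 = 2.973. Power = Φ(2.973 − 1.960) = Φ(1.013) = 84.5%. With pooled variance under the null it is 83.0%.

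**3. Margin in the recruitment target.** 200 − 2 x 100 = 0.

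**4. Effect of loss.** The loss rates are assumptions. Each row treats the lost patients as contributing nothing. The last power column lets DE fall as centres shrink, using an intra-centre correlation (ICC) of (1.4 − 1) / (25 − 1) = 0.0167. That value itself assumes equal centres of 200 / 8 = 25.

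| Complete loss | n per arm | Power, DE 1.4, unpooled | Power, DE 1.4, pooled | Recomputed DE | Power, recomputed DE, unpooled |
|---|---|---|---|---|---|
| 0% | 100 | 84.5% | 83.0% | 1.40 | 84.5% |
| 5% | 95 | 82.6% | 81.0% | 1.38 | 83.1% |
| 10% | 90 | 80.5% | 78.8% | 1.36 | 81.7% |
| 20% | 80 | 75.8% | 73.9% | 1.32 | 78.3% |

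With DE 1.4, keeping 85% after such losses would have meant recruiting 102 / 0.95 = 108, 102 / 0.90 = 114 or 102 / 0.80 = 128 per arm.

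**5. Can the content of 1.4 be recovered?** For unequal centres, DE = 1 + [(1 + CV²) x m − 1] x ICC, where m is mean centre size and CV its coefficient of variation. With m = 25:

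- CV 0: ICC = 0.4 / 24 = 0.0167
- CV 0.5: ICC = 0.4 / 30.25 = 0.0132
- CV 0.6: ICC = 0.4 / 33 = 0.0121

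All three give 1.4. The factor is therefore compatible with equal centres and with clearly unequal ones.

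The same holds for families. Suppose each patient in a centre of 25 had one relative there with correlation 0.2. Then DE = 1 + 0.2 + 23 x ρ, which is 1.4 when unrelated patients correlate at ρ = 0.2 / 23 = 0.0087. The document's figures cannot separate these cases.

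**The case against.** The strongest reply is that no arithmetic error has been shown. The plan's inputs reproduce its own number, and every lower power comes from a loss rate that the document does not give. That is true, and the size of the shortfall is conditional. The absence of a margin is not: it follows from 101.6 needed, 100 stated and 200 recruited.

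A second reply is that the primary outcome is a yearly count followed to the end of follow-up or death and analysed by intention to treat, so leavers may still contribute. This also stands. If a lost 10% gave half their information (an assumption), the effective loss would be 5% and power about 82.6% rather than 80.5%. The figures in the table are therefore a worst case.

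A third reply is that a journal article commonly leaves the ICC and the attrition assumption to the full protocol. That is a reason not to treat their absence as an error in itself. It does not remove the point that a specific power is stated for a number that equals the recruitment target.

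A reader might go further and infer that unequal centres and family correlation push power well below 85%, for instance to about 73% once assumed values for both are stacked on a 10% loss. The document does not support this. Step 5 shows that 1.4 may already include unequal sizes. Relatives followed at the same centre already form part of the within-centre correlation, so adding a family term on top may count them twice. The document does not say how many relatives were enrolled or whether they share a centre.

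**Conclusion.** The point holds in a limited form. The stated sample size is exhausted by the two proportions and the factor of 1.4, and the recruitment target adds nothing, so the 85% has no allowance for the withdrawal the plan itself foresees. Even with no loss the power is 84.5% (unpooled) or 83.0% (pooled). With 1.4 held fixed and unpooled variance, complete loss of 5% to 20% takes it to between 82.6% and 75.8%. These figures rest on assumed loss rates, on lost patients contributing nothing, and on the plan's two rates being accepted as proportions.

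On unequal centres and family correlation, all that can be said is that 1.4 is not shown to cover them. Whether they lower power further cannot be determined. A flat statement that 100 per arm fails to deliver 85% because of them would go beyond the document.

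**What to change.** In Sample size calculation, restate the power for the number expected to complete 2 years. Recruitment is complete (Trial status), so the design effect can be derived from the actual centre sizes and a total within-centre ICC that includes relatives at the same centre. Add a separate family term only for families not already counted in that ICC, to avoid double-counting.

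If this is not done, state two assumptions of the calculation: that no patient is lost, and that 1.4 covers all within-centre and family correlation.

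Do not write instead that 85% holds given equal centres, no relatives and no loss. Eight centres leave 6 degrees of freedom between clusters. With the standardised difference of 2.973 as the non-centrality parameter and a critical t of 2.447, power is about 70% even under those conditions.

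The cost is one recalculation and one sentence. No extra patients are needed; the downside is a less favourable stated power.

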### Statistical analysis

Descriptive analyses will provide the following information for each continuous variable: mean value, standard deviation, 95 % confidence interval (CI), minimum, first quartile, median, third quartile and maximum and number of missing observations. Categorical variables will be expressed as numbers and percentages.

#### Analysis of primary outcome

The number of admissions for angioedema attacks will be analysed in the intent-to-treat population.

Because some patients may be blood relatives and because data from within the same family are not independent, the analysis will use generalised mixed models with the family included in the model as a random effect, the strategy as a fixed effect and with a binomial distribution of the variable of interest.

All tests will be two-sided.

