### Participating centers

Eight French reference centres for bradykinin-mediated angioedema are participating in the trial. The centres were accredited in 2006 by the French Ministry of Health. Their mission is to improve access to diagnosis and therapy for patients with HAE. All eight centres have medical and paramedical teams with experience in the field of HAE, all implement a therapeutic education programme based on guidelines for systematic treatment of severe attacks and for prophylaxis of recurrent attacks, and all offer nurse-led sessions on self-administration of specific therapy for an attack [2, 3, 8, 15].

The freephone call centre ([name]) is hosted by the French emergency medical service (EMS) of a Paris suburb (SAMU 93) which has the logistics capabilities needed to provide 24/7/365 expert medical advice over the telephone [16]. SAMU 93 has promoted appropriate care of HAE attacks by (1) posting placards in SAMU 93 to enhance awareness and (2) providing their emergency physicians with instruction sheets on recommended emergency management of HAE attacks and prophylaxis of recurrence [2].

In France, each local EMS is equipped with one or more mobile intensive care units (MICUs), which include a senior emergency physician, a nurse and an ambulance driver. MICUs provide rescue techniques and medical advice, known as advanced life support, throughout France [16]. The local EMS facilities of each participating reference centre have the required logistics capabilities for storage and around-the-clock delivery of appropriate specific agents (plasma-derived C1-INH and icatibant) to patients or healthcare organisations [17]. If the case is life-threatening, SOS-HAE will immediately contact SAMU headquarters.

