### Data collection and follow-up

#### Medical data

HAE specialists and emergency physicians collect standardised clinical data including those presented in the most recent Hereditary Angioedema International Working Group (HAWK) guidelines [2]:On day zero (D0): Patient sex, age, type of HAE (type I, II or FXII-HAE), time since diagnosis, personal history of angioedema (ED visits during previous year, admissions to intensive care unit (ICU) and history of intubation and tracheotomy), ongoing long-term treatment and number of relatives with HAEAt each attack and every 2 months for 2 years: Number of attacks and, for each attack: possible trigger of attack, day and time of onset of symptoms, day and time of call to SOS-HAE centre, edema site, home therapy (self-administered or caregiver) or hospital treatment, time treatment started and course of attack (onset of symptom relief and time of symptom resolution)Number of admissions/patient/year over 2 years, duration of admissions, number of admissions to ICU/patient/year over 2 years, number of ED visits/patient/year over 2 years, number of intubations, number of interventions by EMS and mortality

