### Outcome measures

#### Primary outcome

The primary outcome is the number of admissions for angioedema attacks per patient per year over a 2-year period. The number of admissions for angioedema attacks is measured from the randomisation date until the end of follow-up or death. For patients discharged alive, information on the primary outcome will be collected by phoning the patients. All admission observation charts are collected and collated.

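### The stated primary model omits the prior-year ED visits recorded at D0 and the centre-size stratum, so it cannot correct a chance severity imbalance between eight centres; the precision gain from adding them is uncertain

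*Protocol article*

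**What the plan says.** The protocol article (Analysis of primary outcome) writes the primary model out term by term: "the analysis will use generalised mixed models with the family included in the model as a random effect". Its single fixed effect is the study arm, and the outcome is taken as binomial. No baseline covariate, size stratum or centre term is named there, and no other section adds one.

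Two other sections bear on this:

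- Medical data lists, among the items recorded on D0, "ED visits during previous year", together with ICU history, HAE type and long-term treatment.
- Randomisation describes "randomisation stratified according to the number of eligible HAE patients by reference centre", with whole centres allocated 1:1 in blocks of four. Under Participating centers: "Eight French reference centres for bradykinin-mediated angioedema are participating in the trial".

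The outcome is a count: "The primary outcome is the number of admissions for angioedema attacks per patient per year over a 2-year period".

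**The concern.** Past hospital use for attacks is a natural predictor of later admissions. The sample size section itself works with ED visits and admissions together. Stratifying by centre size balances size, not severity. With so few randomised units, the two sets of centres can differ by chance in how ill their patients are, and a model holding only strategy and family attributes that difference to the call centre. The variable that could correct part of it is already in the case report form. The analysis also does not follow the stratified randomisation.

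**Working it through.** **The plan's own sample size.** Inputs from Sample size calculation: 88% v 68%, two-sided 5%, 85% power, design effect 1.4. With unpooled variance:

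- 0.88 × 0.12 + 0.68 × 0.32 = 0.3232
- n = 0.3232 × (1.960 + 1.036)² / 0.20² = 72.5
- 72.5 × 1.4 = 101.6 per arm, close to the stated 100.

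With 200/8 = 25 patients per centre, a design effect of 1.4 implies an ICC of 0.4/24 = 0.017.

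**Chance imbalance in a baseline covariate.** The documents give no ICC for prior-year ED visits, so the outcome's design effect is borrowed first and then varied. SD of the arm difference, in covariate SDs = √(2 × design effect / 100).

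| Covariate ICC (assumed) | Design effect | SD of difference | P(≥ 0.2 SD) | P(≥ 0.3 SD) |
|---|---|---|---|---|
| 0.017 | 1.4 | 0.167 | 23% | 7% |
| 0.05 | 2.2 | 0.210 | 34% | 15% |
| 0.10 | 3.4 | 0.261 | 44% | 25% |

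At a covariate-outcome correlation r, an imbalance of 0.2 SD shifts the unadjusted outcome difference by about 0.2r SD. That is 0.04 SD at r = 0.2 and 0.10 SD at r = 0.5, against a standard error of 0.167 SD for the outcome difference.

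**Precision on a count or rate scale.** The documents give no correlation. Assume a gamma-Poisson model with annual rate μ, shape k, a one-year baseline and a two-year follow-up, in which both periods count the same kind of event:

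- covariance = 2μ²/k; baseline variance = μ + μ²/k; follow-up variance = 2μ + 4μ²/k; variance reduction = r².
- μ = 0.88 (from "i.e. an estimated 88 % per year", which covers ED visits or admissions): k = 0.5 gives r = 0.70 and 50%; k = 2 gives r = 0.38 and 14%.
- μ = 0.3 (assumed, for admissions alone): k = 0.5 gives r = 0.45 and 20%; k = 2 gives r = 0.17 and 3%.

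ED visits are only a proxy for admissions, so the lower end is more realistic. The reduction applies to patient-level variance, and to between-centre variance only as far as the covariate explains it.

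**Precision on a logit scale.** The stated distribution is binomial and no link is named. I simulated the same gamma-Poisson scenarios with 100 patients per arm, no clustering, any admission over two years as outcome, log(count + 0.5) as covariate and a rate ratio of 0.68/0.88 = 0.773. At 0.88 per year and k = 0.5, the standard error of the strategy coefficient rose from 0.284 to 0.331 (0.331/0.284 = 1.17). The coefficient itself also grew, because adjustment targets a conditional odds ratio. At 0.88 per year, power moved by about one percentage point. At a larger effect (rate ratio 0.5, my assumption) adjustment raised power by about 2 to 9 points at that rate. Adjustment did not lower power in any scenario.

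**Stratum term.** No gain can be computed, because neither the cut-offs nor the link between centre size and outcome is given. Its cost, if there are two strata and the analysis respects eight centres, is one of about 6 between-centre degrees of freedom: the t critical value goes from 2.45 to 2.57, about 5% on the interval width.

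**The case against.** The other side has several good points.

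- **An unadjusted comparison is valid in a randomised trial, and this is a condensed article.** Both are true, and a fuller document could add covariates. But the article lists the model's terms rather than leaving them open, so adding terms would depart from what is written.
- **A reader might infer that omitting the covariate widens the confidence interval, perhaps by the full 14% to 50% in variance computed at 0.88 per year.** The documents do not support that. They specify a binomial distribution, and with a logit link the interval for the log odds ratio does not narrow. The 0.88 figure also mixes ED visits with admissions. Under Definitions, an ED visit is a consultation without admission, so on that definition the covariate excludes the outcome event.
- **The imbalance probabilities borrow a design effect.** This stands, and they are conditional on that assumption.
- **The stratum half is weak.** Stratification already limits imbalance in centre size, and omitting a prognostic stratum normally makes the test conservative rather than liberal. The reason to include it is consistency with the randomisation.
- **Covariates do not repair the larger fault in the same sentence.** The randomised unit, the centre, is not in the model. If the family effect absorbed none of the centre clustering, a design effect of 1.4 would raise the two-sided error to about 9.8% (1.96/√1.4 = 1.656). This stands, so the covariates belong beside a centre effect, not in place of one.
- **D0 history is not recorded blind.** Under Randomisation, D0 follows centre allocation, and Blinding says physicians and nurses know the arm. This is a real but minor caveat.

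**Conclusion.** The point holds as a modest, inexpensive improvement. The stated model leaves out a relevant baseline measure that the trial collects and a factor that the randomisation used, so it cannot correct a severity imbalance between the two groups of centres. Such an imbalance is plausible: about 23% for at least 0.2 SD at the borrowed design effect of 1.4, and more if prior ED use clusters more strongly by centre.

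A reader might go further and call the unadjusted estimate biased. Over the randomisation it is not; the issue is a chance difference in the one allocation that is realised. Nor is a definite precision gain established. It ranges from about 3% to 50% of variance on a count or rate scale under assumed heterogeneity, while on a logit scale there is no narrowing and little change in power at the planned rates. A split of four centres against four is inferred from eight centres at 1:1 in blocks of four; the article does not print it.

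**What to change.** Before outcomes are analysed by arm, amend the primary model to include:

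1. prior-year ED visits from D0 as a fixed effect, for example as log(count + 0.5);
2. the centre-size stratum as a fixed effect, with its cut-offs stated, so that the analysis follows the randomisation;
3. a centre effect with a small-sample correction, since items 1 and 2 do not account for the randomised unit.

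Keep the analysis without covariates as a sensitivity analysis, and state whether the strategy effect is reported on a rate or an odds scale, because an adjusted odds ratio answers a different question from an unadjusted one.

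Cost: analysis wording only, since the data are already collected. The patient-level covariate uses almost no information. The stratum term uses one of about 6 between-centre degrees of freedom if there are two strata. Because D0 history is recorded once staff know the allocation, verify prior-year ED visits against hospital records where possible.

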#### Analysis of secondary outcomes

Secondary outcomes will be analysed using a mixed model ANOVA. The family will be introduced into the model as a random effect. All tests will be two-sided.

Number of admissions for a cause other than an angioedema attack per year for 2-year-period, mortality from an angioedema attack, mortality from another cause, number of ICU admissions per year, number of ED admissions per year, number of hospital stays, number of intubations per year, number of interventions by EMS, number of working days lost (and duration), costs (hospital and ambulatory costs) of patient care and SF-36 will all be estimated in each arm for 2 years.

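### The primary and secondary models leave out reference centre, the randomised unit, so any between-centre correlation makes the stated 5% test anti-conservative (about 9.8% at the plan's own design effect of 1.4)

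*Protocol article*

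**What the plan says.** The protocol article, under Randomisation, makes the centre the unit of allocation: "The randomised units are the reference centres (clusters) with randomisation stratified according to the number of eligible HAE patients by reference centre". Under Participating centers it gives the number: "Eight French reference centres for bradykinin-mediated angioedema are participating in the trial". The Abstract gives the target: "The trial aims to recruit 200 patients". That is an average of 25 patients per centre.

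The Sample size calculation section recognises correlation within centres. It takes the "design effect due to cluster randomisation as relatively low (1.4" and arrives at 100 patients per arm for 85% power at a two-sided 5% level, comparing 88% with 68%.

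The Analysis of primary outcome section then specifies "generalised mixed models with the family included in the model as a random effect, the strategy as a fixed effect", with a binomial distribution. The only reason given for the random effect is that some participants may be blood relatives. For the secondary outcomes the article says: "The family will be introduced into the model as a random effect". No analysis section puts reference centre in a model or names another way of allowing for it.

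**The concern.** Clustering by centre is allowed for in the sample size and then dropped from the analysis. Every patient in a centre has the same strategy, so the uncertainty of the strategy effect has to come from how much centres differ from one another, and there are only eight. The stated model takes that uncertainty from families and patients instead.

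A family effect is no substitute. It gives two unrelated patients of the same centre a correlation of zero, whatever they share in clinicians, patient education or local emergency services. If centres differ at all for reasons other than strategy, standard errors are too small, confidence intervals too narrow and false-positive findings more frequent than 5%. This applies to the primary comparison and to every secondary comparison, costs included.

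**Working it through.** **Inputs from the article.** 8 centres; 200 patients, 100 per arm; design effect (DE) 1.4; 88% against 68%; power 85%; two-sided 5%. The binary scale is used below only because the plan's sample size uses it.

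**1. The plan's own figure.** Two proportions, unpooled variance:

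- Variance sum = 0.88 × 0.12 + 0.68 × 0.32 = 0.1056 + 0.2176 = 0.3232.
- n = (1.960 + 1.036)² × 0.3232 / 0.20² = 72.5 per arm.
- 72.5 × 1.4 = 101.6 per arm.

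This agrees with the stated 100 to within 3%, so 1.4 was in fact used. At 25 patients per centre (assuming equal centres) it implies an intraclass correlation of 0.4 / 24 = 0.017.

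**2. Type I error when centre is left out.** If the true variance of the effect is DE times what the model assumes, the actual two-sided level is 2 × [1 − Φ(1.96 / √DE)]. This takes the family term as absorbing none of the centre variance.

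| DE | Actual level |
|---|---|
| 1.1 (assumed) | 6.2% |
| 1.2 (assumed) | 7.4% |
| 1.4 (the plan's value) | 9.8% |
| 1.6 (assumed) | 12.1% |
| 2.0 (assumed) | 16.6% |

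At the plan's value: 1.96 / √1.4 = 1.656, and 2 × [1 − Φ(1.656)] = 0.098.

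**3. Does the family term help?** This was checked by simulation on a continuous scale: 8 centres of 24 patients, centre correlation 0.0167, 20,000 null trials per setting. The document gives no family sizes or family correlation, so both are assumed.

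- Every patient a family of one: about 9.7%.
- Families of 2 to 4 with an added family correlation of 0.1 to 0.5: 7.2% to 9.3%, lowest where the family correlation was strongest.
- Centre-level t-test on 6 df, same data: 4.8% to 5.4%.

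**4. Is a centre effect enough by itself?** No. With equal-sized centres and a standard error estimated from eight centre means, the test statistic follows a t distribution on 8 − 2 = 6 df. Compared with 1.96 it rejects with probability P(|t₆| > 1.96) = 9.8%. That this matches the figure in step 2 is a coincidence. The correct critical value is 2.447.

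**5. Power with correct inference.**

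- Standard error = √(0.3232 × 1.4 / 100) = 0.0673.
- Noncentrality = 0.20 / 0.0673 = 2.97.
- Normal test: Φ(2.97 − 1.96) = 84.5%, the plan's 85%.
- t on 6 df (critical value 2.447): 69.9%.
- t on 5 df (critical value 2.571), if a centre-level size-stratum term is added: 66.5%.

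**The case against.** The strongest objection is to stating the inflation as a fact. A reader might infer that the planned test simply has a 10% error rate. The document does not support that. The 1.4 is a planning assumption, introduced conditionally, and no between-centre variance is reported. Admissions may also be spread over many local hospitals rather than the reference centres, which could weaken the centre effect. The simulation, moreover, uses a continuous outcome, equal centres and assumed families, and does not fit the binomial model that the article names. All of this stands as a limit on the size. It does not change the direction, because any positive centre correlation inflates the error.

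A second objection is that model details belong in an analysis plan that is not shown. That would excuse silence, but the article is not silent. It names the random effect and gives a reason for it that concerns kinship, not the design.

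Two further readings go too far. One is that leaving out the size stratum or the previous year's emergency department visits is an error of the same kind. It is not: both are optional covariates, and omitting them does not invalidate the test. The other is that a permutation test could not reach 5%. With two strata of four centres there would be 6 × 6 = 36 allocations and a smallest two-sided p of 2/36 = 0.056. The article states blocks of four but not the number of strata, so this holds only under that assumption.

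**Conclusion.** The point holds: the stated primary and secondary models contradict the randomisation and the sample size of the same article, and the error is anti-conservative. At the plan's own design effect the nominal 5% test runs at about 9.8% if family absorbs no centre variance, and at roughly 7-9% under assumed strong family correlation. With an assumed design effect of 1.1 it is 6.2%. The true figure depends on a centre correlation that the document does not give. This needs correcting before the analysis, because it bears on the primary test.

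**What to change.** - In both analysis sections, add reference centre as a random effect alongside family, with strategy as the fixed effect. Do not assume that families are nested in centres unless it is confirmed that none spans two.
- Base inference on between-centre degrees of freedom: 6, or 5 if a size-stratum term is added. Use a mixed model with a small-sample correction or a centre-level analysis. If the latter uses log rates, say in advance how a centre with no admissions is handled. Do not use a normal-based Wald test.
- Treat the size stratum and the previous year's emergency department visits as optional covariates, and settle the choice before unblinding.
- Restate the power on the plan's own assumptions: about 70% with 6 df or about 66% with 5 df, in place of 85%.

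The change itself is analysis work and wording, with no new data. The real cost is wider confidence intervals and lower power than advertised. Trial status reports that recruitment is complete, so the sponsor should be told plainly that the loss cannot be made up by enrolling more patients.
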